#### Adherence to cues and musicality.

Adherence will be treated both as a continuous variable (percentage change in cadence from baseline) and as a binary variable for group comparisons. The primary binary adherence definition is: adherent = ≥5% increase in cadence from baseline; non-adherent = < 5%. Mann–Whitney U tests will compare Gold-MSI between adherent and non-adherent participants. Participants with missing baseline or intervention-based cadence (e.g., wishing to withdraw or technology failure) will be excluded from binary adherence analyses and numbers excluded will be reported.

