If assumptions for normality are not met, a Friedman test will be used to assess within-subject differences across cueing conditions. Post-hoc Wilcoxon signed-rank tests, with Bonferroni correction, will be conducted only if the Friedman test is statistically significant. For between-subject effects (e.g., walk order), where normality assumptions are violated, the Kruskal–Wallis test will be used to assess group-level differences between walk-order groups. Interaction effects between cueing and walk order will be explored non-parametrically by conducting separate Friedman tests within each walk order group. Effect sizes for non-parametric tests will be calculated using the rank-biserial correlation coefficient, $\text{r}=\text{Z}/\sqrt{\text{N}}$, providing a measure of the magnitude of the effects observed.

For the three primary comparisons, we will control the familywise error rate using a Bonferroni adjustment. Given three cueing modalities, statistical significance (*p*) will be evaluated at a two-sided α = 0.01/3 = 0.0033. Effect sizes (i.e., SRM) and 95% confidence intervals will also be reported. Secondary and exploratory analyses (e.g., comparing cueing modalities to one another, examining washout effects, assessing stride-to-stride variability) will not be subject to multiplicity correction. For these analyses, a two-sided *p*-value of 0.05 will be considered statistically significant across all parametric and nonparametric tests.

To assess whether the first cue produced short-term residual effects, we will calculate changes in gait outcomes from baseline to each cued walk and from each cued walk to its subsequent washout walk (WO1 and WO2). For each cue exposure, a carryover score will be calculated as the difference between the change induced by the cue and the change observed during the corresponding washout period, reflecting retained cue effects. The approach enables an evaluation of carryover effects after each cued walk separately, thereby capturing any cumulative or progressive retention of cueing effects. Group differences based on initial cue type (i.e., counterbalanced sequence) will be evaluated using one-way ANOVA or the Kruskal–Wallis test, depending on normality assumptions [74–80].

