### Primary objectives: Validity and evaluating the effects of personalised auditory cues on gait

The impact each personalised auditory cue has on participants’ stride length, gait speed, and${\text{ CV}}_{\text{stride}-\text{time}}$ are a significant exploratory interest. These metrics, in particular${\text{ CV}}_{\text{stride}-\text{time}}$, where a decrease is known to reduce the risk of falling, have indicated variable effects among PwPD in other cueing-related studies, particularly where music cueing is not personalised [9,44,73]. The findings from this study will establish a baseline understanding of their (i) validity (from an app and smartphone worn on the lower back) and (ii) whether personalised cues can consistently reduce stride variability across a broader range of participants.

Observed gait responses will be interpreted in the context of sequence-conditional effects (cue order, exposure, and adaptation over time), and not as definitive evidence of causal superiority of one cueing condition over another. Analyses of gait variability and asymmetry will be interpreted cautiously, as these measures typically exhibit greater dispersion and may be underpowered (as sample size of based on gait speed). Emphasis will be placed on estimating effect sizes and examining consistency of responses across conditions, rather than on formal hypothesis testing.

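### The non-parametric effect size is named rank-biserial but defined as Z/√N, a different statistic that leaves N undefined and cannot be applied to the Friedman and Kruskal–Wallis tests

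*Protocol article*

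**What the plan says.** The Statistical analysis section sets out what happens when normality fails. First, "a Friedman test will be used to assess within-subject differences across cueing conditions". Then: "Post-hoc Wilcoxon signed-rank tests, with Bonferroni correction, will be conducted only if the Friedman test is statistically significant". For order effects, "the Kruskal–Wallis test will be used to assess group-level differences between walk-order groups". The interaction of cue and order is explored by "conducting separate Friedman tests within each walk order group". The paragraph closes with: "Effect sizes for non-parametric tests will be calculated using the rank-biserial correlation coefficient", and gives r = Z/√N as its formula. The sentence is not limited to any one of these tests, N is not defined as pairs or observations, and no other effect size is named for the omnibus tests.

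One further rank test appears under Adherence to cues and musicality, where Mann–Whitney U "tests will compare Gold-MSI between adherent and non-adherent participants". That section names no effect size of its own.

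**The concern.** A named statistic and a formula that does not produce it are joined in one rule. An analyst who follows the name and one who follows the formula will report different numbers from the same data, and both will call the result rank-biserial. A reader who sets the value beside a true rank-biserial from another study would compare unlike quantities.

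The rule also reaches tests for which it has no input, so it cannot be carried out there as written. This has some weight because the Discussion says "Emphasis will be placed on estimating effect sizes and examining consistency of responses across conditions", and because the Statistical analysis section itself expects the coefficient of variation of stride time to be skewed, so the rank-based route may well be used.

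**Working it through.** The plan gives no figure to reproduce here, so the check is whether the rank-biserial equals Z/√N.

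**Inputs.** 60 participants are recruited and up to 10% attrition is allowed (Sample size), so 60 × 0.9 = 54 may remain. There are 20 participants per sequence (Walking/gait tasks). The planning SRM is 0.5 (Sample size). There are three cue conditions and three order groups.

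**Wilcoxon signed-rank, no ties.**
- Rank-biserial: r_rb = (W+ − W−)/(W+ + W−), with W+ + W− = n(n+1)/2.
- Z = (W+ − n(n+1)/4)/√(n(n+1)(2n+1)/24).
- Hence Z/√n = r_rb × √(1.5(n+1)/(2n+1)).
- n = 60: √(1.5 × 61/121) = √0.7562 = 0.870.
- n = 54: √(1.5 × 55/109) = √0.7569 = 0.870.
- If N is read as observations (2n), divide by √2: 0.870/1.414 = 0.615.

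Direct check at n = 60 with every difference in one direction: W+ exceeds its null mean by 60 × 61/4 = 915. The null SD is √(60 × 61 × 121/24) = 135.84. So Z = 6.74 and Z/√60 = 0.870, while r_rb = 1.

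**At the planned effect.** Simulating 20,000 samples of 60 normally distributed differences with SRM 0.5 gives these means:

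| Quantity | Mean |
|---|---|
| Rank-biserial | 0.52 |
| Z/√n | 0.45 |
| Z/√(2n) | 0.32 |

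**Mann–Whitney, no ties.** The rank-biserial is 2U/(n1·n2) − 1, which runs from −1 to 1 for any split. The maximum of Z/√N is √(3·n1·n2/(N(N+1))). The splits below are assumptions, since the article cannot know how many participants will adhere; N = 54.

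| Split | Ceiling of Z/√N |
|---|---|
| 27/27 | √(2187/2970) = 0.86 |
| 40/14 | √(1680/2970) = 0.75 |
| 45/9 | √(1215/2970) = 0.64 |

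The same complete separation of musicality scores would therefore give a different r for each cue if the adherent fraction differed by cue. Ties in the questionnaire scores would raise these ceilings slightly.

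**Friedman and Kruskal–Wallis.** With three conditions or three groups, each returns an unsigned chi-square on 2 degrees of freedom, so there is no Z to enter. A makeshift √(chi-square/N) does not rescue the rule. The Friedman statistic can reach N(k − 1) = 2N, so the makeshift value could reach √2 = 1.41, which is not a correlation.

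**The case against.** The strongest reply is that little hangs on this number.

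- **SRM is already the main effect size.** The Statistical analysis section has SRM calculated for cadence, stride length, gait speed and stride-time variability with no condition on normality, and ties it with 95% confidence intervals to the three primary comparisons. A reader might infer that Z/√N carries the interpretation whenever normality fails. The article does not support that, and the Discussion's emphasis on effect sizes fits SRM at least as well. This part of the reply stands.
- **The analyses concerned are mostly secondary.** The Friedman and post-hoc Wilcoxon tests compare cues with one another, which the same section classes as secondary or exploratory, and the Discussion treats musicality as exploratory. This stands.
- **Z/√N is a legitimate statistic under its own name.** A reader might infer that effects will be understated. They are smaller only relative to the statistic named. For paired data at fixed n without ties the two differ by a constant, so direction and ranking of cue effects do not change, and the article sets no interpretation bands for this r. This stands.
- **The sentence may be meant only for the Wilcoxon tests, and an omnibus effect size may be left to a fuller plan.** This stands only in part. Silence on an omnibus measure would be no fault, but the sentence speaks of non-parametric tests without limit, directly after the omnibus tests, so it states a rule that cannot be followed. Even on the narrow reading, name and formula disagree and N is undefined. Extending the sentence to Mann–Whitney is a reading, and the figures for that test are conditional on it.

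**Conclusion.** The rule is wrong as written, with a small consequence. For the signed-rank tests the reported value would be about 0.87 of the statistic it is called, or about 0.61 if N is taken as observations. At an SRM of 0.5 that is roughly 0.45 or 0.32 in place of 0.52. If Mann–Whitney is covered, the scale also depends on the adherence split. For Friedman and Kruskal–Wallis the formula has no input.

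These figures assume data without heavy ties, which is reasonable for continuous gait outcomes; with every absolute difference tied, a tie-corrected Z/√N could reach 1. The SRM comparison further assumes normal differences. What is affected is effect-size reporting in fallback and mostly secondary analyses. The primary comparisons keep SRM with its interval, and no test result, significance threshold or sample size is touched.

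**What to change.** Make name and formula agree, in one of two ways:

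1. Keep the rank-biserial name and replace the formula with (W+ − W−)/(W+ + W−) for Wilcoxon and, if an effect size is wanted there, 2U/(n1·n2) − 1 for Mann–Whitney.
2. Keep r = Z/√N, drop the rank-biserial label, and state whether N counts pairs or observations.

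Either way, restrict the measure to two-condition or two-group tests, and give the omnibus tests a measure of their own, such as Kendall's W for Friedman and epsilon-squared for Kruskal–Wallis. The choice between the two routes is a matter of preference.

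The cost is one or two sentences in the Statistical analysis section. No data collection, test or threshold changes.

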#### Sample size.

Sample size calculations were based on detecting changes in gait speed using a within-subject design. Assuming a standardised response mean (SRM) of 0.5 (moderate effect size) for gait speed, a two-sided significance level (α) of 0.01, and 90% power, approximately 54 participants would be required to detect a statistically significant change in gait speed for a single comparison (e.g., cued vs. non-cued walking). When accounting for the three cueing conditions and the associated adjustment for multiple (three) comparisons, we applied a Bonferroni correction resulting in an adjusted alpha of α (0.01/3 = 0.0033). That requirement increases sample size to approx. 55 participants. However, to allow for an anticipated attrition rate of up to 10%, we plan to recruit 60 participants in total. This sample size ensures adequate power to detect moderate cueing effects on gait speed, accommodates potential dropouts, and provides balanced representation across randomisation sequences.

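### Single-step Bonferroni for the three primary comparisons is valid, but Holm's step-down keeps the same 1% familywise error and gives more power when at least two cues work

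*Protocol article*

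**What the plan says.** The Statistical analysis section of the protocol article sets the rule: "For the three primary comparisons, we will control the familywise error rate using a Bonferroni adjustment". Significance "will be evaluated at a two-sided α = 0.01/3 = 0.0033". Effect sizes and 95% confidence intervals are to accompany the tests.

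The Sample size section uses the same rule. It starts from "Assuming a standardised response mean (SRM) of 0.5 (moderate effect size) for gait speed", with "a two-sided significance level (α) of 0.01, and 90% power", and states that "approximately 54 participants would be required to detect a statistically significant change in gait speed" "for a single comparison (e.g., cued vs. non-cued walking"). For three cues, "we applied a Bonferroni correction resulting in an adjusted alpha of" 0.0033, and the requirement becomes about 55. Sixty are to be recruited to allow for up to 10% attrition.

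The three primary comparisons are not listed one by one. The Sample size section gives cued against uncued walking as its example, and the Statistical analysis section puts cue-against-cue tests among the secondary analyses: "comparing cueing modalities to one another, examining washout effects, assessing stride-to-stride variability) will not be subject to multiplicity correction". The natural reading is therefore metronome, instrumental music and vocal music, each against the baseline walk, on gait speed. No step-down procedure is mentioned, and no reason is given for testing in a single step.

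**The concern.** Single-step Bonferroni holds every comparison to 0.0033 even after one or two of the others have been rejected. By then fewer hypotheses can still be falsely rejected, so the full division by three is no longer needed to protect the 1% familywise rate. Holm uses this fact and Bonferroni does not.

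The study has a fixed size and wants a separate answer for each cue. A cue with a p-value between 0.0033 and 0.01 could be declared effective under Holm and not under Bonferroni, at the same error rate and on the same data. What is at stake is avoidable loss of power, not the validity of any conclusion.

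**Working it through.** **Inputs from the protocol article.** SRM 0.5; familywise α = 0.01, two-sided; three comparisons; stated power 90%; stated n of 54 (one comparison) and 55 (after Bonferroni); 60 recruited, leaving 60 × 0.9 = 54 after 10% attrition.

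**Input not in the document.** The correlation ρ between the three change scores. They share one baseline. If all four walks have variance σ² and pairwise correlation r, each change has variance 2σ²(1 − r), and two changes have covariance rσ² − rσ² − rσ² + σ² = σ²(1 − r). The ratio is 0.5. I take 0.5 as the central assumption and show 0 to 0.9.

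**Step 1: the plan's own figures.** α = 0.01/3 = 0.0033 is right. The sample sizes do not reproduce. With n = ((z for α/2 + z for power)/SRM)²:
- α = 0.01: ((2.576 + 1.282)/0.5)² = 59.5, so 60; 63 with the t distribution. Stated: 54.
- α = 0.0033: ((2.935 + 1.282)/0.5)² = 71.1, so 72; 76 with t. Stated: 55.

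Power per comparison under Bonferroni, from the noncentral t with noncentrality 0.5√n, is 72.2% at n = 54, 73.4% at n = 55 and 78.7% at n = 60.

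**Step 2: why Holm is safe.** Order the p-values and compare them with 0.01/3 = 0.0033, 0.01/2 = 0.005 and 0.01, stopping at the first failure. If m of the nulls are true, the first of them to be rejected must have p ≤ 0.01/m. By the union bound that happens with probability at most m × 0.01/m = 0.01, whatever the correlation. No threshold is below 0.0033, so nothing that Bonferroni rejects is lost.

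**Step 3: size of the gain.** Simulation of 60,000 trials per scenario: trivariate normal change scores, three paired t-tests, familywise α = 0.01. Entries are power in %, Bonferroni → Holm, with SRM 0.5 for all three cues.

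| n | ρ | Per comparison | All three |
|---|---|---|---|
| 54 | 0 | 72.2 → 80.4 | 37.7 → 57.5 |
| 54 | 0.5 | 72.1 → 79.0 | 49.1 → 65.2 |
| 54 | 0.9 | 72.2 → 77.3 | 62.5 → 73.9 |
| 55 | 0.5 | 73.5 → 80.2 | 51.4 → 67.0 |
| 60 | 0 | 78.6 → 86.1 | 48.6 → 67.6 |
| 60 | 0.5 | 78.8 → 85.0 | 59.0 → 73.8 |
| 60 | 0.9 | 78.7 → 83.2 | 70.3 → 80.3 |

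The gains are about 4 to 8 points per comparison and 10 to 20 for all three. Power for at least one rejection does not change (92.0% at n = 55, ρ = 0.5), because both methods have the same first step.

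**Step 4: if not every cue works (ρ = 0.5).**
- Two cues at SRM 0.5, one at 0: at n = 54, 72.2 → 75.1 per real effect and 57.9 → 63.8 for both; at n = 60, 78.6 → 81.1 and 66.5 → 71.6.
- One cue at 0.5, two at 0 (n = 55): 73.7 → 73.7.
- SRMs of 0.5, 0.4 and 0.3 (n = 55): gains of 2.0, 6.2 and 8.8 points, and 14.9 → 25.9 for all three.

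**Step 5: error check (n = 55, ρ = 0.5).** Simulated familywise error under Holm is 0.92% with all three nulls true, 0.77% with two and 0.70% with one.

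**The case against.** Bonferroni is valid, prespecified, correctly computed as 0.01/3 and consistent between the Sample size and Statistical analysis sections. A reader might infer from this point that the plan contains an error of inference. It does not: the choice costs power and nothing else.

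The gain is conditional. The abstract itself expects heterogeneous responses that may be neutral or adverse, so three equal effects are not assured. A flat promise of about 7 points per comparison and 15 for all three would be the favourable case stated as fact. Nor is rejection of all three comparisons a success criterion in the protocol; the per-comparison gain is closer to what the Sample size section plans for.

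Bonferroni also has simple matching simultaneous intervals, and the Discussion puts estimation ahead of formal testing. This has some weight. But the intervals promised are 95%, whereas intervals matched to 0.0033 would be 99.67%, so the plan does not use that advantage. The Statistical analysis section also keeps a formal familywise rule, and while it stands the more powerful form is preferable.

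Two further inferences should be resisted. Holm does not repair the sample size: 55 against the 72 to 76 that the plan's own inputs require is a separate and larger problem. And Holm does not help to say which cue is best, because cue-against-cue comparisons lie outside the primary family.

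**Conclusion.** The point stands as an efficiency improvement, not as the correction of an error. That Holm controls the same 1% familywise error and never rejects less than Bonferroni needs no assumption about correlation or effects. The size of the benefit does: roughly 4 to 8 points per comparison and 10 to 20 for all three if every cue has SRM 0.5, about 3 and 5 to 6 if two cues work, and none if one works. The correlation is assumed, since the protocol gives none.

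The stated 90% is not reached either way. At ρ = 0.5, per-comparison power under Holm is about 79% at n = 54 and 85% at n = 60.

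**What to change.** In the Statistical analysis section, replace the Bonferroni sentence and its 0.0033 threshold with wording such as: Holm step-down at two-sided familywise 0.01 (0.0033, 0.005, 0.01) for the three cue-versus-baseline comparisons of gait speed. Naming the outcome matters, because that section lists four outcomes and a step-down needs a fixed family. The same thresholds apply to p-values from the non-parametric fallback. The 0.0033 in the Sample size section can stay as the first-step level; the numbers of participants derived from it need separate correction.

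The change relaxes a rejection rule, so it must be made and documented before outcome data are analysed. The Recruitment section has recruitment ending in December 2025 and results in February 2026; if analysis has already begun, the prespecified Bonferroni rule should stay. The change should be reported to the trial registry, as the Data management and availability section provides for significant protocol changes.

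The cost is one sentence and that report, with no extra participants or data. The only statistical price is the lack of a simple matching simultaneous interval.

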Therefore, the primary objectives of this protocol are to (i) validate gait characteristics from CuePD and (ii) evaluate the effects of personalised auditory cues (metronome beats, instrumental music, and vocal music) to retrain and improve gait in a lab, i.e., increase gait speed, cadence and stride length while reducing gait variability. Our secondary objectives are to assess recruited PwPD and their (a) acceptance and preference of personalised music cues compared to traditional metronome cueing while (b) understanding their ability to adhere to cues due to their musicality.

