A two-way mixed ANOVA will be used to assesses the effects of cueing modality and walk order on outcomes, i.e., cadence, gait speed, stride length, and CV_stride-time_. Comparable to the referenced PD study, cueing modality will be modelled as a within-subject factor, while walk order as a between-subject factor to account for potential sequence effects. For each outcome, within-participant changes from baseline will be calculated using cue-specific difference scores. To account for differences in scale and statistical distribution among the outcomes, change scores will be computed using Equations (30)-(31):

Percentage change of gait speed and stride length from baseline, calculated as:

$$\%\Delta =\frac{\text{Cue Value}-\text{Baseline Value}}{\text{Baseline Value}}\times \text{1}\text{0}\text{0}$$
(30)

In contrast,${\text{ CV}}_{\text{stride}-\text{time}}$, a dimensionless ratio-based variable that may have a skewed distribution, change will be computed using the natural log-ratio of cue value to baseline:

$$\Delta_{log}=\text{log}\left(\text{Cue Value}+\in \right)-\text{log}\left(\text{Baseline Value}+\in \right)$$
(31)

where 𝜖 is a small constant to avoid the logarithm of zero. This transformation was chosen as ${\text{CV}}_{\text{stride}-\text{time}}$ is a ratio-based measure that can be highly skewed and exhibit unequal variances across conditions. Applying the *log* transformation to change scores helps to normalise the distribution and stabilise the variance, thereby supporting more reliable statistical comparisons of cueing effects on ${\text{CV}}_{\text{stride}-\text{time}}$ in this within-subjects design. Post-hoc comparisons between cueing modalities will be conducted using paired t-tests, with Bonferroni correction applied to account for multiple comparisons. Effect sizes will be reported using Cohen’s d.

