To evaluate the relationship between musical sophistication and response to cueing, two sets of analyses will be conducted using Gold-MSI subscale scores. Assumption checks, including the Shapiro-Wilk test and Q-Q plot inspections, will be used to assess the distribution of change scores prior to both analyses. First, the association between Gold-MSI scores and cue adherence (defined as the absolute deviation from a + 10% target increase in cadence) will be assessed using Spearman’s rank correlation coefficient, with Bonferroni correction for multiple comparisons across subscales. Second, associations between Gold-MSI scores and gait outcome improvements (percentage change in gait speed and stride length, and log-ratio change in ${\text{CV}}_{\text{stride}-\text{time}}$) will also be tested using Spearman’s correlation, with Bonferroni correction.

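### Between-cue tests are given two different significance thresholds, and the three primary comparisons are set without naming their outcome

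*Protocol article*

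**What the plan says.** All threshold rules are in the Statistical analysis section of the protocol article.

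- Between-cue tests, parametric path: "Post-hoc comparisons between cueing modalities will be conducted using paired t-tests, with Bonferroni correction applied to account for multiple comparisons".
- Between-cue tests, non-parametric path: "Post-hoc Wilcoxon signed-rank tests, with Bonferroni correction, will be conducted only if the Friedman test is statistically significant".
- Later, among examples of secondary and exploratory analyses: "comparing cueing modalities to one another, examining washout effects, assessing stride-to-stride variability) will not be subject to multiplicity correction". For these, "a two-sided *p*-value of 0.05 will be considered statistically significant across all parametric and nonparametric tests".
- Primary tests: "For the three primary comparisons, we will control the familywise error rate using a Bonferroni adjustment", and "statistical significance (*p*) will be evaluated at a two-sided α = 0.01/3 = 0.0033". The divisor is justified by the number of cueing modalities. No outcome is named.
- Gold-MSI correlations with cue adherence: "with Bonferroni correction for multiple comparisons across subscales". The Gold-MSI correlations with gait outcomes are Bonferroni-corrected as well.

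The second primary objective, in the Introduction, covers several measures: "increase gait speed, cadence and stride length while reducing gait variability". The mixed ANOVA is applied to the same four (cadence, gait speed, stride length and CV of stride time). The Sample size section is based on gait speed alone. It gives cued versus non-cued walking as its example comparison and uses the same 0.01/3.

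**The concern.** Comparing the cues with one another is how the study would say whether music does better or worse than a metronome. The Impact of cueing section sets out to identify which cue works best. For those tests an analyst following the article finds an instruction to correct and an instruction not to correct. The second covers both parametric and non-parametric tests, so it cannot be read as applying to only one path. The rule could then be chosen after the p-values are known, which prespecification is meant to prevent.

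The second issue is which tests are primary. Three comparisons at 0.0033 form a complete family only if there is one outcome. The primary objective lists four, and one of them (variability) is placed among the secondary and exploratory analyses when thresholds are set. A reader cannot tell whether a cadence or stride-length result is to be judged at 0.0033 or at 0.05.

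**Working it through.** **Inputs from the article.** Primary alpha 0.01 two-sided, divided by 3; secondary alpha 0.05 two-sided; three cues, hence three cue pairs per outcome; four outcomes in the ANOVA; 60 participants planned.

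**1. The plan's own figure.** 0.01/3 = 0.00333, which agrees with the stated 0.0033. Three tests at that level give at most 3 × 0.00333 = 0.010 (0.00997 if independent). The arithmetic is right for a family of three.

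**2. Thresholds for one between-cue test.**

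| Rule followed | Threshold |
|---|---|
| Waiver | 0.05 |
| Bonferroni on 0.05 | 0.05/3 = 0.0167 |
| Bonferroni on 0.01 | 0.01/3 = 0.0033 |

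The Bonferroni sentences do not say which alpha is divided. Taking 0.05, the disputed range is 0.0167 to 0.05. For example, music versus metronome at p = 0.02 is significant under the waiver and not under the correction. Taking 0.01, the range widens to 0.0033 to 0.05.

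**3. Familywise error for the three pairs, per outcome.**

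- Uncorrected and treated as independent: 1 − 0.95³ = 0.143.
- The three differences are linked, because any two determine the third. A null simulation of the three paired t-tests (40,000 runs, n = 60, three equally variable conditions) gives 0.123.
- With Bonferroni at 0.05/3: 1 − (1 − 0.0167)³ = 0.049 if independent; 0.045 in the same simulation.

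The 12% applies to the paired t-test path, where no omnibus gate is stated. On the non-parametric path the Wilcoxon tests run only after a significant Friedman test. With three conditions, either all three pairs are null, and the gate limits the error, or at most one pair is null, and it is tested once. Gated, uncorrected tests at 0.05 therefore stay near 5% per outcome, assuming the Friedman test is itself judged at 0.05.

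**4. The primary family if more than one outcome is meant.** The threshold paragraph places variability among the 0.05-level analyses. That leaves at most three outcomes for 0.0033: gait speed, cadence and stride length.

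- 3 outcomes × 3 cues = 9 tests.
- Bound: 9 × 0.00333 = 0.030; if independent, 1 − (1 − 0.00333)⁹ = 0.0296.
- To hold 0.01 over nine tests, each would need 0.01/9 = 0.0011.

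With gait speed alone the family is three tests and 0.0033 is correct.

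**The case against.** The strongest defence is that the study is exploratory. The Discussion says gait responses will not be taken as definitive evidence that one cue is superior, and it puts effect sizes ahead of formal testing. That stands and lowers the severity. It does not tell the analyst which rule applies, because the Statistical analysis section still fixes thresholds for these tests. Nor does condensation into an article explain the conflict: it can drop detail, but here two opposite instructions are both printed.

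Several stronger readings are tempting and are not supported:

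- *The claimed familywise control fails.* The plan claims control only for three primary comparisons. If these are gait speed, as the Sample size section implies, 3 × 0.0033 delivers it. The fault is that the outcome is not named.
- *Twelve primary tests at 0.0033, so 4%.* The plan describes no such family, because variability is assigned to 0.05. Cadence is unsettled too: it is in the objective and the ANOVA but absent from the Impact of cueing section and the Conclusion. An objective that lists several measures does not make each one a primary comparison.
- *A variability result at p = 0.02 is both significant and not significant against baseline.* Only one threshold, 0.05, is stated for it. The objective sets no alpha.
- *A 46% chance of a false between-cue finding.* That figure is 1 − 0.95¹² = 0.46. It treats twelve linked tests as independent and ignores the Friedman gate.
- *The Gold-MSI rule contradicts the waiver.* The waiver's examples do not include Gold-MSI, so its Bonferroni rule can stand as a specific exception to a general default. It needs tidying only.

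**Conclusion.** The contradiction over between-cue tests is real and can be read directly from the text. It decides significance for any p-value from 0.0167 to 0.05, assuming the correction divides 0.05. Following the waiver raises the familywise error to about 12% per outcome on the paired t-test path, against about 4.5% with Bonferroni. These two figures rest on a simulation with 60 participants and equally variable conditions. On the Friedman-gated path the difference is small.

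The primary comparisons are under-defined, though not wrongly computed. The stated 1% holds if gait speed is the sole primary outcome. It could rise to 3.0% if the same threshold were also used for cadence and stride length. Variability is part of the primary objective but is treated as secondary or exploratory when thresholds are set, and the two places should agree.

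This should be fixed, but it is not critical: the clear conflict concerns comparisons on which the plan already declines to draw definitive conclusions.

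**What to change.** In the Statistical analysis section:

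1. State that the three primary comparisons are cued versus uncued gait speed, one per cue, each at two-sided 0.0033. This matches the outcome used in the Sample size section.
2. Label stride length, cadence and CV of stride time as secondary, and make the Introduction, Discussion and Conclusion agree.
3. Keep Bonferroni for the between-cue post-hoc tests on both paths and state the level: 0.05/3 = 0.0167 per outcome.
4. Remove the between-cue comparisons from the list of uncorrected analyses. Reword the waiver so that it covers only other secondary and exploratory analyses, except where a correction is specified, namely the between-cue post-hoc tests and the Gold-MSI correlations.

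The design and data collection do not change. Some between-cue results will face a stricter threshold. The correction holds per outcome only: over four outcomes the bound is 4 × 0.05 = 0.20, which is acceptable for secondary analyses if said openly. Settling the outcome labels is more than an edit of wording. It may need a registry update, since the Data management section commits to reporting significant protocol changes there. The change should be dated before the between-cue results are seen. If they have already been seen, report them against both thresholds.
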